#### Intervention resources

The *Guidelines *include reviews of the current referral practices and utilisation of palliative care services in Australia; patients' physical, psychological, social/cultural, spiritual and financial/legal issues; as well as caregivers/families' and health professionals' issues [6].

The NAT: PD-C aims to operationalise the *Guidelines *and includes four sections:

1. Section 1 includes three items to fast-track a review by a specialist palliative care service: the absence of a caregiver (if one is needed), a patient or caregiver request for referral to a specialist palliative care service, and the health professional's need for assistance in managing care;

2. Section 2 assesses the patient's wellbeing, and includes physical, daily living, psychological, information, spiritual/existential, cultural and social, financial and legal domains;

3. Section 3 assesses the ability of the caregiver/family to care for the patient, and includes physical, daily living, psychological, information, financial and legal and family and relationship domains;

4. Section 4 assesses the caregiver's own wellbeing, including physical, psychological and bereavement issues.

For Section 1, response options are "Yes" or "No". Items in Sections 2-4 are assessed according to the level of concern ("none", "some/potential for", "significant") they were causing. Prompt questions for each item were included on the back page, to facilitate consistency in how issues were addressed. Each item has a set of tick boxes to indicate the action taken ("directly managed", "managed by another care team member", "referral required") to address any identified needs. Finally, should a referral be required, the NAT: PD-C includes a section detailing the type of referral made (eg to specialist palliative care service, social worker, general practitioner, medical oncologist), the urgency of the referral ("urgent", "semi-urgent", "non-urgent") and client knowledge of the referral.

Once the training is completed at a particular site, the outpatient clinic appointment dates of each patient participant will be identified. Prior to each appointment, the research nurse will place a copy of the NAT: PD-C in the medical record of the patient; and will send an email to each clinician at the beginning of the week with a list of patients due to have NAT: PD-Cs completed at the next appointment. Health professionals at participating sites will be asked to complete NAT: PD-Cs in consultation with the patient, at every appointment for each patient participant, or approximately monthly if appointments are more frequent. Staff members of specialist palliative care services and allied health professionals will also be asked to complete the NAT: PD-C on each of the patients referred to them at initial assessment and, subsequently, monthly whilst they remain in contact with that patient. Finally, GPs will be sent a letter requesting that they complete the NAT: PD-C at the patient's next appointment, with remuneration offered to cover the extended consultation time.

### Analysis

Descriptive statistics of patient characteristics at baseline and summary measures of their level of need, anxiety, depression and quality of life at each time point will be presented as means and 95% confidence intervals for continuous variables and as proportions and 95% confidence where the data were categorical. The patients' baseline interview scores for each of these outcomes will be examined to determine whether scores varied according to age, gender, presence of a caregiver and level of care giving provided to them. Statistical significance will be assessed using chi square tests for categorical variables and t-tests for continuous outcomes (α = 0.05).

#### Changes in primary and secondary outcomes over time

For each patient, level of need, anxiety, depression and quality of life will be measured repeatedly during the study and therefore a Generalised Estimating Equation (GEE) model will be used to analyse the data [39]. In this study the GEE model will fit time as a factor and also analyse the number of CATIs completed as an interaction variable. Age, gender, time since diagnosis, co-morbidity score and presence of a caregiver will be included as potential confounding variables for patient participants. Age and gender will also be included as confounder for caregiver participants. For the purpose of this study, presence of a caregiver will include patients who had a participating caregiver at first assessment as well as patients who subsequently indicated they had a caregiver in any of their CATIs (irrespective of whether their caregiver consented to participate). GEEs will be run for both continuous and categorical outcome variables adjusting for the potential confounders listed above to ascertain whether the intervention had any impact on patient and caregiver outcomes.

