**Methods/design:**

People with advanced cancer and their caregivers completed bi-monthly telephone interviews over a period of up to 18 months to assess unmet needs, anxiety and depression, quality of life, satisfaction with care and service utilisation. The intervention, introduced after at least two baseline phone interviews, involved a) training medical, nursing and allied health professionals at each recruitment site on the use of the *Palliative Care Needs Assessment Guidelines *and the Needs Assessment Tool: Progressive Disease - Cancer (NAT: PD-C); b) health professionals completing the NAT: PD-C with participating patients approximately monthly for the rest of the study period. Changes in outcomes will be compared pre-and post-intervention.

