### Study design

The study utilises an interrupted time series design [14], with data collected at multiple time points before and after the intervention is introduced [15]. By collecting data before and after the intervention, researchers can determine whether the intervention has an effect significantly greater than the underlying secular trend [15,16]. One advantage of this design is that it allows both the short-term and long-term effects of the intervention to be examined more akin to an effectiveness study than a more limited efficacy study [14]. Moreover, this design is highly suited for use in smaller populations and complex interventions [14].

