### Materials

Participants will complete bi-monthly CATIs over a period of 18 months. Primary outcomes include patient and caregiver unmet needs and patient service utilisation. Secondary outcomes include patient and caregiver anxiety, depression and quality of life and caregiver satisfaction with care.

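### The stated GEE identifies no intervention term, so as worded it does not separate the intervention from the secular trend that the interrupted time series design was chosen to address

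*Protocol article*

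**What the plan says.** All references are to the protocol article.

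- **Study design** gives the reason for an interrupted time series: "researchers can determine whether the intervention has an effect significantly greater than the underlying secular trend".
- **Abstract, Methods/design** states the comparison: "Changes in outcomes will be compared pre-and post-intervention". The intervention is "introduced after at least two baseline phone interviews". The Sample size section also describes the main outcome as before and after percentages.
- **Changes in primary and secondary outcomes over time** gives the model: "In this study the GEE model will fit time as a factor and also analyse the number of CATIs completed as an interaction variable". It continues: "Age, gender, time since diagnosis, co-morbidity score and presence of a caregiver will be included as potential confounding variables for patient participants". For caregivers the adjustment is age and gender. The GEEs are then meant "to ascertain whether the intervention had any impact on patient and caregiver outcomes".
- **Service utilisation and referral patterns** assesses change over time in the number of health professionals seen, again by GEE, and names no phase term. Service utilisation is a primary outcome under Materials.
- **Intervention resources** ties the start of NAT: PD-C use to each site: "Once the training is completed at a particular site, the outpatient clinic appointment dates of each patient participant will be identified".
- **Materials** sets the follow-up: "Participants will complete bi-monthly CATIs over a period of 18 months".

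**The concern.** There is no control group, so the whole case for a causal reading rests on separating the intervention from what would have happened anyway. In advanced cancer, needs, distress and service use can be expected to move as the disease progresses. To deliver what the Study design section promises, the model needs a term for the underlying course and a separate term for the change when the intervention starts. The listed terms are time as a factor, the number of interviews completed in some interaction, and patient characteristics. None is identified as the intervention, yet the model is said to show whether the intervention had an impact.

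The error can go either way. Natural drift can be credited to the intervention, or drift in the opposite direction can hide a real benefit.

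**Working it through.** **1. The plan's own figure.** Inputs from Sample size: 50% falling to 40%, 5% significance, 80% power. For two independent proportions, two-sided:

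n = [1.96·√(2·0.45·0.55) + 0.8416·√(0.25 + 0.24)]² / 0.10² = 387.3 per group.

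With continuity correction: (387.3/4)·[1 + √(1 + 4/(387.3·0.10))]² = 407.09. The stated 407 is reproduced. It is a plain comparison of two proportions with no trend term, so it does not supply what the model lacks.

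**2. The two readings of time.**

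| Reading | What the coefficients estimate |
|---|---|
| Interview wave | Disease trajectory and intervention added together |
| Before/after | A before/after difference, with no trend clearly removed |

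**3. Can a phase term be added to a wave factor?** Assume one interview every two months: 18/2 = 9 waves. Nine wave columns have rank 9.
- All patients switch at the same interview: adding a post indicator leaves the rank at 9 of 10 columns, so the two are aliased.
- Patients switch at interviews 3, 4 and 5: rank 10 of 10, so a post term is estimable.

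**4. Size of the mixing (illustration).** Number the waves 0 to 8, with 2 before and 7 after. The mean wave is 0.5 before and 5.0 after, a gap of 4.5. Assume variance 0.25, exchangeable correlation 0.5, 407 patients, no attrition and no true effect.

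SE = √[0.25·(1 − 0.5)·(1/2 + 1/7)/407] = 0.0141.

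Rejection rate = Φ(δ/SE − 1.96) + Φ(−δ/SE − 1.96), with δ = 4.5 × drift:

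| Drift per wave | Spurious difference δ | Rejection rate (nominal 5%) |
|---|---|---|
| 0.5 points | 2.25 points | 36% |
| 1 point | 4.5 points | 89% |

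A drift of 10/4.5 = 2.2 points per wave would by itself produce the whole 10-point target.

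**5. Simulation.** Assumed: 407 patients, 9 interviews, start after the third, logit random intercept SD 1, no dropout, 200 runs per setting.
- No effect, drift −0.05 logit per interview: a before/after contrast built from the wave factor was significant in 77.5% of runs, and a trend-plus-step GEE in 3%.
- No effect, four drift settings (0, −0.05, −0.10, +0.05): trend plus step rejected in 9.5%, 3%, 5% and 3.5% of runs. That is 42 of 800, or 5.25%.
- True effect −0.47 logit with opposing drift +0.10: the wave-factor contrast detected it in 7.5% of runs, trend plus step in 95.5%.

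**6. Power of the possible repairs.** Var(β) = (Σ XᵢᵀV⁻¹Xᵢ)⁻¹, V = 0.25·[(1−ρ)I + ρJ], 407 patients, no attrition. Power is for a 10-point level change. Ranges run from ρ = 0.3 to ρ = 0.5.

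| Switch | Terms | SE | Power |
|---|---|---|---|
| Staggered over interviews 3–5 | wave factor + level | 0.033–0.029 | 85.0–93.9% |
| Staggered over interviews 3–5 | wave factor + level + slope change | 0.035–0.030 | 82.5–91.0% |
| All at interview 3 | linear trend + level | 0.024–0.020 | 98.6–99.8% |
| All at interview 3 | linear trend + level + slope change | 0.048–0.041 | 54.1–68.5% |

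With an assumed 10% loss per wave, the second row falls to about 72–83% and the fourth to about 49–63%.

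**The case against.** The strongest defence is that the model sentence is ambiguous. It does not say whether time is wave or before/after, whether the number of interviews is a patient's total or a running count, or what it interacts with. If time were before/after and the count a running one, their interaction, together with a main effect of the count, would be a segmented model with level and slope change. The article also names a before/after comparison elsewhere, and a fuller protocol or analysis plan may define the contrast.

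Much of this stands. A reader might infer that the planned GEE cannot separate intervention from trend. The text does not support that. A phase term is estimable if starts are staggered, and a contrast against an extrapolated baseline trend could be built, although two baseline interviews estimate a trend weakly. What the text supports is narrower: the model as worded does not identify the intervention term. The way the analysis sections speak of time points favours the wave reading. The point also does not rest on silence, because the article does state a model and its purpose, and the two do not match.

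Three other inferences go too far.
- Staggered starts do not leave wave and exposure wholly unaligned. With switches at interviews 3, 4 and 5, waves 1–2 are entirely before and 5–9 entirely after, so 7 of 9 line up.
- The article implies that each site's training completion is known operationally, but never says the date is recorded.
- The 36% and 89% are not properties of the plan. The article gives no drift figure and specifies no pooled contrast, and patients with advanced cancer will be lost. With an assumed loss of 10–30% per wave, the pooled gap falls from 4.5 to 4.1–3.3 waves.

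**Conclusion.** The concern holds in this form: the stated model does not name the term that would test the intervention against the secular trend, although that separation is the stated reason for the design. Followed as a wave-factor model, it mixes trajectory and intervention. Followed as a before/after model, it does not clearly remove the trend. The same applies to the service-use GEE.

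That mixing does not depend on any assumed number, but its size does. The rejection rates of 36% and 89% rest on assumed drift, 9 interviews split 2 and 7, correlation 0.5 and no attrition. They show only that modest drift is enough to matter. The point is important because it concerns the test of the study's central question. It is a matter of specification, not a fatal flaw in the design.

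**What to change.** In the sections on changes in outcomes over time and on service utilisation, replace the model sentence with a GEE containing:

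1. an underlying time term;
2. a post-intervention indicator, equal to 1 for every interview on or after training completion at the patient's site, whether or not a NAT: PD-C was completed;
3. time since the switch, as a secondary slope-change term.

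Name the level-change coefficient as the primary test, and say whether it comes from the model with or without item 3. Keep the wave factor only if patients switch at different interview numbers. If all switch at the same number, use a linear or smooth time term. State what the number of interviews completed means and what it interacts with.

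**Cost.** The change is to the analysis text, but site training-completion dates must reach the analyst, and their availability should be confirmed. A linear trend is itself an assumption. Precision falls relative to a naive before/after comparison: on the stated assumptions, power for 10 points ranges from about 99% (common switch, linear trend plus level) down to 54.1–68.5% (common switch, slope change added), and is lower with attrition. That spread is the reason to fix the terms before the outcome data are analysed.

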## Sample size

The main outcome of interest in this study is each patient's level of unmet needs as measured by the Supportive Care Needs Survey - Short Form (SCNS-SF34) [17]. The percentage of people reporting at least one moderate or high need in each of the domains in the SCNS was calculated pre- and post-intervention. Having a moderate or high need was chosen as the category indicating a need as it has been suggested that "by evaluating psychosocial interventions with patients experiencing moderate to severe symptoms, future research is likely to yield findings of greater relevance to clinical practice" [18]. A systematic review of unmet supportive care needs in people with cancer reported that a number of studies have used a classification of moderate or high need to assess the prevalence of needs in people with cancer [19]. Many of these studies have reported prevalence for individual items (range 2-48%) rather than the prevalence of people with at least one need in each domain [20-23]. A recent study reported that the percentage of people with cancer identified as having at least one moderate or high need for help using the of the SCNS-SF34 ranged from 15% (sexuality domain) to 53% (psychological domain) [17]. Six spiritual items from the Needs Assessment for Advanced Cancer Patients (NA-ACP) [24]; a 132 item instrument assessing the needs of people with advanced incurable cancer [24], were assessed using the same response options as the SCNS.

Assuming a maximum prevalence of 50% (worst case scenario) at pre-intervention for all domains, it was calculated that using a 5% significance level and having a minimum of 407 patients would give the study 80% power to detect a reduction in prevalence of 10% in each of the five SCNS-SF34 domains and one NA-ACP domain post-intervention. However, this estimation of expected change in prevalence could not be supported by any previous literature, as few studies have looked at changes in needs over time or changes in the prevalence of needs resulting from an intervention [19].

Caregivers of all consenting patients will also be invited to participate in the study. Of an estimated 407 patients consenting to participate, it is anticipated that 60% will have a consenting caregiver (n = 245).

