### Procedure

Participants will be recruited from the medical oncology, radiation oncology and haematology outpatient clinics from three major cancer centres in NSW, Australia. Initially, a research nurse will review clinic lists to identify patients who meet eligibility criterion (1). The list will then be reviewed by a clinician or clinic nurse to exclude patients who do not meet eligibility criteria (2), (3) and (4) and to make the initial approach to eligible patients. The research nurse will then provide a verbal and written explanation of the study to patients interested in the study and obtain their informed consent to participate. Consenting participants will be asked to nominate a caregiver and if the caregiver is present at the clinic at the time of recruitment, the research nurse will provide them with a verbal and written explanation of the study. If not, the caregiver information will be given to the patient who will be asked to pass it on to the caregiver. If the patient is unable to nominate a caregiver at the time of recruitment, s/he will be asked during the first and subsequent computer assisted telephone interviews (CATIs) to nominate a caregiver in case their circumstances change during the course of the study.

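### The GEE adjustment list omits centre although the intervention starts centre by centre, so between-centre differences in need can bias the pre/post estimate

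*Protocol article*

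**What the plan says.** Under Procedure, the protocol article recruits from "medical oncology, radiation oncology and haematology outpatient clinics from three major cancer centres". Under Intervention resources, use of the assessment tool is set in motion "Once the training is completed at a particular site", so the switch from the pre- to the post-intervention phase is tied to the centre. The Abstract requires at least two baseline interviews before the intervention and sets no upper limit. It describes the comparison as pre versus post, and no concurrent control is described.

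Under Changes in primary and secondary outcomes over time, the GEE fits time as a factor, with the number of interviews completed as an interaction variable. The covariates are then listed: "Age, gender, time since diagnosis, co-morbidity score and presence of a caregiver will be included as potential confounding variables for patient participants". Caregiver models get age and gender. The section closes by saying that the impact of the intervention will be judged from models adjusted for the confounders it has just listed. Centre does not appear in that list, in the baseline comparisons described under Analysis, or in the Sample size section.

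**The concern.** Centre determines when a patient's exposure changes, and it may also be related to need through case mix and access to services. A variable with both properties is a confounder of the pre/post contrast. If a high-need centre contributes relatively more pre-intervention interviews, the pooled data show a fall in need that the intervention did not cause. If a low-need centre does so, a real benefit is partly hidden. The estimate at stake is the primary one, unmet need before and after the intervention, and the same models serve the secondary outcomes and the caregivers.

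This is more than a detail left to a fuller document, because the article states the covariate list and ties the intervention estimate to it.

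**Working it through.** **1. The plan's own figure.** Inputs from Sample size: 50% prevalence before, 40% after, 5% significance (two-sided assumed, since sidedness is not stated) and 80% power.

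- Two independent proportions: n = [1.96·√(2·0.45·0.55) + 0.8416·√(0.50·0.50 + 0.40·0.60)]² / 0.10² = (1.379 + 0.589)² / 0.01 ≈ 387.3, or 388 rounded up.
- With continuity correction: n' = (n/4)·[1 + √(1 + 4/(n·0.10))]² = 96.8 × (1 + 1.0504)² ≈ 407.1.

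This reproduces the stated "a minimum of 407 patients" (408 if rounded up). The formula contains no centre term. It also gives the yardstick: a planned effect of 10 points, or a log odds ratio of ln(0.40/0.60) − ln(0.50/0.50) = −0.41.

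**2. Mixing of centres with no true effect, unweighted.** Let p be the prevalence of need in a centre and s the share of its interviews that fall before the switch, with centres contributing equal numbers of interviews. Then pooled pre = Σps/Σs and pooled post = Σp(1−s)/Σ(1−s). The document gives none of these values, so all are assumptions.

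| Centre prevalences (%) | Pre shares (%) | Pooled pre | Pooled post | Apparent change |
|---|---|---|---|---|
| 60/50/40 | equal in all centres | 50% | 50% | 0 |
| 60/50/40 | 40/33/25 | 0.505/0.98 = 51.5% | 0.995/2.02 = 49.3% | −2.3 points |
| 60/50/40 | 50/33/20 | 0.545/1.03 = 52.9% | 0.955/1.97 = 48.5% | −4.4 points |
| 60/40/50 | 50/33/20 | 0.532/1.03 = 51.7% | 0.968/1.97 = 49.1% | −2.5 points |
| 50/60/40 | 50/33/20 | 0.528/1.03 = 51.3% | 0.972/1.97 = 49.3% | −1.9 points |
| 40/50/60 | 50/33/20 | 0.485/1.03 = 47.1% | 1.015/1.97 = 51.5% | +4.4 points |

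The last row shows the opposite direction.

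**3. What a GEE does with it.** Simulations with no true effect used 407 patients, three equal centres, nine interviews, 10% dropout per interview and a patient random-effect SD of 1 on the logit scale (150 runs per setting). In every setting the higher-need centre switched later.

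- *Phase only (pre/post), centre omitted, 2/3/4 baseline interviews.* With exchangeable correlation, centres at 40/50/60% gave a mean log odds ratio of −0.06 and 13% false positives; centres at 45/50/55% gave −0.03 and 5%. With an independence working correlation the false-positive rates were 39% and 12%.
- *Interview number as a factor plus a phase indicator, centre omitted, 3/4/5 baseline interviews.* With exchangeable correlation, 40/50/60% gave −0.23 and 25%; 45/50/55% gave −0.13 and 12%. With independence the results were −0.58 and 87%, and −0.30 and 35%.
- *The second model with centre added.* The mean log odds ratio was about 0 and false positives were 5–6%.

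With 150 runs, the Monte Carlo standard error of a 13% rate is √(0.13·0.87/150) = 2.7 points, so small differences between these rates should not be read closely.

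**The case against.** The strongest reply is that the risk is conditional. Bias needs centres to differ in need and also in their pre/post shares. The document gives no training dates, centre sizes or centre prevalences, and the site-level wording describes a procedure without saying that centres switched at different interviews. This stands, and it limits the conclusion to what can happen.

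It is also fair that 4.4 points is an unfavourable case. It orders need and pre-share in parallel. A 20% pre-share is at or below the floor, since two baselines out of nine interviews is 22% and dropout raises the share. A 60% centre lies above the 15–53% range that Sample size cites. Centre is constant within a patient, so repeated interviews carry information free of fixed centre differences; exchangeable weighting uses more of it and shrinks the bias. The larger false-positive rates depend on a model with both interview number and a phase indicator, which the article does not spell out. That model separates phase from interview number only through centres switching at different interviews. The simulations also leave out the planned patient covariates, which might absorb part of the centre differences. None of this makes the bias zero in general.

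Three stronger readings are tempting but unsupported:

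- *That the estimate is in fact contaminated.* The document does not show unequal shares.
- *That omitting centre in itself makes the standard error misleading.* Nothing here quantifies that, and centre fixed effects would not repair centre-by-period variation, which is the relevant issue for a change delivered at centre level.
- *That clinic type is confounded with exposure in the same way.* The switch is tied to the site, not to clinic type.

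A last reply is that a condensed article may leave centre terms to a fuller document. The closing reference to the listed confounders weakens that.

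**Conclusion.** The point holds as a conditional weakness in a stated analysis choice. The adjustment set leaves out the unit at which the intervention starts, and nothing in the article ensures that centres contribute equal pre and post shares. If centres also differ in need, the pre/post estimate can be biased in either direction.

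The size is not derivable from the document. It is zero with equal shares and about 2 to 4 points in an unweighted comparison under the assumed prevalences and shares, against a planned 10 points. In a simple pre/post model with exchangeable correlation it was about −0.03 to −0.06 on the log odds scale, against a planned −0.41. It is larger with an independence working correlation, or if phase is estimated alongside interview number. Because the remedy is nearly costless, this is a free improvement; the material does not show that the planned result would be wrong.

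**What to change.** - Add centre (three levels) as a fixed effect in every patient and caregiver GEE.
- Define the pre/post phase for each interview by the training-completion date of that participant's own centre.
- Show the intervention estimate by centre, as description only.
- Do not use robust standard errors clustered on centre; three clusters are too few.
- Clinic type may be added as an optional covariate where it is recorded.

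Cost: 3 − 1 = 2 degrees of freedom and a change of wording. The target of 407 patients is unchanged, and no new data are needed, since centre is known from recruitment.

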### Participants

Inclusion criteria for patients are: (1) having a diagnosis of advanced cancer, ie, no longer amenable to cure, with either extensive local or regional spread, or metastatic disease; (2) being aged 18 years or older; (3) understanding English sufficiently well to complete questionnaires and telephone interviews; and (4) judged by the clinic staff as emotionally and cognitively capable of participating. Caregiver inclusion criteria are: (1) being nominated by the patient as the primary carer or family member who has provided, or may provide when needed, the most help to the patient; and (2) understanding English sufficiently well to complete questionnaires and telephone interviews.

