#### Background questions

Socio-demographic questions will be asked including participant age, gender, marital status, level of education, type of health insurance, gross income and employment. Patients will also be asked about type of diagnosis and time since initial diagnosis; while caregivers will be asked about tasks performed in their care giving role as well as their relationship to and personal contact with the patient. A 12-item index [25] will assess co-morbid conditions, including cerebrovascular disease, inflammatory bowel disease, liver disease, gastric ulcers, arthritis, diabetes, depression, hypertension, chest pain, heart attack, heart failure, and chronic lung disease.

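### The GEE's named patient confounders omit type of cancer, which is collected; if need and loss both differ by cancer, the pre/post contrast can be biased, and the loosely worded interview-count interaction may not remove all of it.

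*Protocol article*

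**What the plan says.** In the protocol article, the section on changes in primary and secondary outcomes over time gives the patient adjustment set: "Age, gender, time since diagnosis, co-morbidity score and presence of a caregiver will be included as potential confounding variables for patient participants". For caregivers it names age and gender. The section closes by saying the GEEs are run "adjusting for the potential confounders listed above to ascertain whether the intervention had any impact on patient and caregiver outcomes", so the adjustment is for a named set. The same section also states that "the GEE model will fit time as a factor and also analyse the number of CATIs completed as an interaction variable".

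Type of cancer is available. Under Background questions: "Patients will also be asked about type of diagnosis and time since initial diagnosis". The second item of that pair enters the model; the first does not.

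The population is mixed. Eligibility requires "having a diagnosis of advanced cancer, ie, no longer amenable to cure, with either extensive local or regional spread, or metastatic disease", with no restriction by site of disease, and patients are "recruited from the medical oncology, radiation oncology and haematology outpatient clinics".

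The abstract states the comparison: "Changes in outcomes will be compared pre-and post-intervention". There is no control group. The abstract also says the intervention follows a minimum of two interviews, and the Intervention section starts it at each site once training there is finished.

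**The concern.** Cancer type does not change within a patient, so it cannot bias a comparison in which every patient gives the same interviews before and after. It can do so when patients are lost. Pre-intervention interviews come first, so a patient lost early contributes mostly or only to the pre period. If patients with some cancers are lost sooner, those cancers make up a smaller share of post-intervention records. If they also carry more, or less, unmet need, prevalence moves between periods with no intervention effect.

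Age, gender, time since diagnosis, co-morbidity and presence of a caregiver are not obvious substitutes for cancer type. If the cancers lost fastest have the most need, the bias looks like benefit. If they have the least need, it hides benefit. Without a control group, nothing else in the design cancels it.

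**Working it through.** **Scale of the target.** The Sample size section gives 407 patients for 50% against 40%, 5% significance and 80% power. Two-sided, independent groups: n0 = (1.960 × √(2 × 0.45 × 0.55) + 0.842 × √(0.25 + 0.24))² / 0.10² = 387.4. With continuity correction: n = (387.4/4) × (1 + √(1 + 4/(387.4 × 0.10)))² = 407.1. The stated figure is reproduced. It serves here only to fix the yardstick of 10 points; this point does not change it.

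**Inputs.** The documents give no need or loss rates by cancer type, so all such rates below are assumptions. All calculations have no true intervention effect.

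**Step 1: shift in mix.** For two equal cancer groups, bias = (post share − pre share of the high-need group) × need gap. Assumptions: 2, 3, 4 or 5 pre-intervention interviews, equally likely; up to 4 afterwards; loss possible after every interview; independence working correlation; expected values.

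| Need, high/low | Retention per interview | High-need share, pre → post | No loss-related term | Count by period | Cancer type in model |
|---|---|---|---|---|---|
| 55/45% | 80/90% | 46.5 → 36.8% | −1.0 | −0.2 | 0.0 |
| 60/40% | 75/93% | 43.7 → 27.3% | −3.3 | −0.5 to −0.7 | 0.0 |
| 65/35% | 70/95% | 41.4 → 20.2% | −6.4 | −0.9 to −1.1 | 0.0 |
| 60/40% | 85/85% | 50 → 50% | 0.0 | 0.0 | 0.0 |

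Second row by hand: (0.273 − 0.437) × 20 = −3.3 points. Ranges in the count column come from averaging the count-specific differences over patients or over post-intervention records. Swapping the need of the two groups reverses every sign.

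**Step 2: why the count term helps, and when it falls short.** If every patient has the same number of pre-intervention interviews and loss is permanent, patients with the same count were interviewed at the same points, so the cancer mix within a count is constant and the bias is zero. In step 1 the number of pre-intervention interviews varies, and with it the number scheduled in total. A count of six may then be a patient who completed two interviews before and four after, or one with five before who was lost after the first interview following the intervention. The first type is mostly from the slowly lost group. In the second row, the high-need share within a count of six is 37.5% of pre records and 29.8% of post records. If everyone were scheduled for the same total (nine, say), the remainder would again be zero.

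**Step 3: false positives with 407 patients.** Simulated GEE, two cancer groups, exactly two interviews before and three after, loss starting after the second, 400 simulated trials per scenario:

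| Need gap; retention | Neither term | Count by period | Cancer type |
|---|---|---|---|
| 20 points; 75/93% | −2.0 points, 11% | 0.05, 4.3% | 0.0, 4.5% |
| 30 points; 70/93% | −4.0 points, 38% | −0.1, 3.7% | −0.05, 5.0% |

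A milder case (10-point gap, 80/90% retention, 250 trials) gave −0.5 points and 6.4% false positives, not distinguishable from 5% with that many trials (standard error √(0.05 × 0.95/250) = 1.4%). An exchangeable working correlation reduced the 20-point case from −2.0 to −1.5 points.

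**The case against.** The strongest reply is that the plan already contains a term aimed at this mechanism. Cancer type is supposed to act through how many interviews a patient gives, and that number is in the model. With a common number of pre-intervention interviews, fitting count by period removes the bias without cancer type, and it covers loss from any cause. This largely stands. It has two limits. The article does not say what the count interacts with, and a minimum of two earlier interviews with a site-by-site start lets the number of pre-intervention interviews vary, so a remainder is possible.

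A second reply also stands: both the need difference and the loss difference are assumed, and the larger figures need strong assumptions.

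A reader might infer that a changing cancer mix will be reported as an intervention effect, in the hoped-for direction, by several points. The documents do not support that. They give neither difference and no direction, and the larger figures describe a model without the count term. A reader might also fault the GEE for number of health professionals seen, in the section on service utilisation. That section lists no covariates at all, so its silence is a matter of condensed reporting and not a stated omission.

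**Conclusion.** The point holds in a conditional form. A collected baseline variable is absent from the named adjustment set of an uncontrolled pre/post model, in a population of mixed cancers. The bias requires that need and loss both differ by cancer type, and it may run either way. Under assumed need gaps of 10 to 30 points with unequal loss, it is about 1 to 6 points with no loss-related term, against the 10-point target. With the count fitted by period it falls to zero if the number of pre-intervention interviews is common to all patients, and to about 0.2 to 1 point if that number and the scheduled total vary as assumed above. With equal loss it is nil. The likely size under the plan as intended is therefore modest. The case for acting rests on how little the protection costs and on the loose wording of the count term.

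**What to change.** Add type of cancer to the named covariates for patient outcomes, in about five or six groups set before analysis, with haematological cancers separate. Use the patient's cancer type in the caregiver models as well. Keep the interview-count term alongside it and state that it enters as count by period, because it also addresses loss unrelated to cancer type.

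Cost: about five extra parameters on about 400 patients, or 80 patients per parameter (400/5), and no new data collection.
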